### Outcomes

Primary outcomes: Change in the symptoms of Attention Deficit/Hyperactivity Disorder and/or Oppositional Defiant Disorder are expected, with a decrease in externalizing symptoms, determined by the Multimodal Treatment Assessment Study—Swanson, Nolan e Pelham (MTA-SNAP-IV) scale: which assesses symptoms of attention deficit/hyperactivity disorder and Oppositional Defiant Disorder in children and adolescents [36]; and by the Kiddie Schedule for Affective Disorders and Schizophrenia for School Aged Children—Lifetime Version (K-SADS-PL, 2013) interview: semi-structured interview that raises important information about the history of psychiatric disorders, at the present time and throughout life and assesses the severity of symptoms [37]. The quantity and intensity of symptoms will be checked and data will be collected before the start of the intervention and again just after the end of the intervention. The MTA-SNAP-IV scale was adapted and has data from the studied clinical group in the Brazilian context [36]. The K-SADS-PL interview is based on the criteria of the most recent version of the Diagnostic and Statistical Manual of Mental Disorders DSMV [10].

Secondary outcomes: Change in parental style are expected with a tendency to democratic style, determined through the Parenting Styles and Dimensions Questionnaire—PSDQ (42 items version): Questionnaire that assesses how parents manage their relationship with their children and the child’s behavior, considering the control dimensions and affection, being based on a theoretical model that categorizes parenting styles into four possible ones: democratic, authoritarian, permissive and negligent. This questionnaire was previously adapted and validated in the Brazilian context [38]. Furthermore, a decrease in the level of perceived stress by caregivers is expected, measured by the Perceived Stress Scale: measures how much individuals perceive situations as stressful. It is a Likert-type scale and contains 14 questions [39], this scale is the most used instrument to assess the perception of stress, having been validated in more than 20 countries, including Brazil [40]. Finally, is expected an improvement in the quality of life of parents and children, determined through two scales: World Health Organization Quality of Life abbreviated measure (WHOQOL-BREF): assesses quality of life. Instrument developed by the World Health Organization, in a version reduced from 100 to 26 items [41] and Kidscreen-52—Version of caregivers’ report and self-report: Evaluates the quality of life of children and adolescents [42]. All scales will be filled before the start of the intervention and again just after the end of the intervention.

### Participant timeline

The participants timeline is shown below, in Fig 2.

**Fig 2 pone.0272516.g002:**
[figure not shown]
Participant timeline.

### Sample size

A sample of 90 participants would be sufficient to detect a small (d = 0.2) to high (0.8) association with a small (0.4) covariance between repeated measures (intraclass correlation coefficient—ICC = 0.9) and an association of moderate (0.5) to high for larger ICCs (0.6 to 0.9).

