Some recent studies evaluated the feasibility of Parent Training implemented through online platforms. In a systematic review on the PT in digital format, several programs were evaluated for their effectiveness, considering that four out of seven programs were originally taught in person and were adapted to the digital format [30]. Of the studies that reported positive behavioral outcomes, the average effect size for parents’ results was d = 0.46 and for results related to children’s behavior, it was d = 0.61 [30]. Rabbitt and colleagues compared two groups of parents, whose children had conduct problems, who went through PT, one undergoing interventions exclusively in person and the other with very little contact between parents and therapists [31]. In both cases, the children showed a significant improvement in terms of functionality, adaptation and reduction of externalizing problems. The study points out, however, that parents reported better satisfaction with the module entirely in person, despite similar effects in all post-treatment assessments [31]. Högström and his collaborators also evaluated the effectiveness of a PT program administered online [32]. The results show a significant decrease in children’s disruptive behaviors, over 18 months, since the beginning of the intervention that lasted 10 weeks. However, parenting skills seemed to worsen over time, demonstrating the need for some type of training maintenance [32]. A meta-analysis study demonstrated that the digital format of parent training promotes significant improvement in children’s behavior when compared to those without treatment [33]. The study also pointed out that interactive computer programs were more effective than non-interactive ones [33]. Another review study demonstrated that the digital format, with reduced professional support, has similar evidence to the traditional format of parent training [34]. In addition, when compared to an untreated group, self-directed programs achieved significant improvements in the child’s behavior (children <9 years, d = 0.47–0.80, 4 studies; and adolescents d = 0.17, 0.20, 2 studies) [34]. Preliminary indicators also suggested that improvements in technology may increase the involvement and results of standard treatment [34].

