### Trial design

The PT trial is designed as a randomized, controlled, experimental, open, single center, equivalence trial, with three-arm parallel groups. Randomization will be performed as block randomization with a 1:1 allocation.

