### Interventions

#### Interventions

Participants will be randomly assigned to either control or one of the experimental groups with a 1:1 allocation as per a computer-generated randomization schedule stratified by children’s age using five permuted blocks of 6 participants.

**GROUP 01:** 30 participants. Conventional treatment, without complementary treatment. Bi-monthly consultations with a child and adolescent psychiatrist, including drug treatment if there is a clinical indication (at medical discretion, according to the clinical protocol), and without any other type of complementary treatment.

**GROUP 02:** 30 participants. Conventional treatment and behavioral intervention in face-to-face format. Bi-monthly consultations with a child and adolescent psychiatrist, including drug treatment if there is a clinical indication (at medical discretion, according to the clinical protocol), and complementary behavioral intervention: parent management training, in face-to-face format, with a specialized therapist, in six sessions held on a weekly basis, adapted from the “Parent Management Training” manual developed by Alan Kazdin [22].

**GROUP 03:** 30 participants. Conventional treatment and behavioral intervention in online format. Bi-monthly consultations with a child and adolescent psychiatrist, including drug treatment if there is a clinical indication (at medical discretion, according to the clinical protocol), and complementary behavioral intervention: parent management training, in online format, on a platform developed for the study, in six modules, to be carried out on a weekly basis, adapted from the “Parent Management Training” manual developed by Alan Kazdin [22].

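### The sample-size statement claims that 90 families can detect d = 0.2, but comparisons between arms of 30 have only about 11 to 42% power for it, and its correlation figures contradict each other

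*Protocol article*

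**What the plan says.** The Sample size section of the protocol article is one sentence with two scenarios.

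- First scenario: "A sample of 90 participants would be sufficient to detect a small (d = 0.2) to high (0.8) association with a small (0.4) covariance". The ICC attached to this scenario, in brackets, is 0.9.
- Second scenario: "an association of moderate (0.5) to high for larger ICCs (0.6 to 0.9".

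The section names no test, alpha, sidedness or power.

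The Interventions section gives each of the three groups the same size. Usual care, for example, is described as "30 participants. Conventional treatment, without complementary treatment". Trial design adds: "Randomization will be performed as block randomization with a 1:1 allocation". The Outcomes section has two measurement times, one before and one just after the intervention. The Objectives ask for before-after comparisons within each training format and for a comparison between formats.

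The Background cites a review of digital parent training in which, among studies with positive outcomes, "the average effect size for parents’ results was d = 0.46 and for results related to children’s behavior, it was d = 0.61".

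**The concern.** An effect of d = 0.2 is small, and 30 families per arm is a small trial. The two fit together only if something unusual is assumed, and the assumption printed beside the claim is itself unclear. One scenario carries both 0.4 and 0.9 as its measure of dependence between repeated measures. The scenario set against it as having larger ICCs runs from 0.6 to 0.9, so it cannot exceed the first if 0.9 is meant.

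The stake is how the result is read. The protocol calls the trial an equivalence trial and will check whether the two formats have similar effects. If 90 families could detect d = 0.2, a non-significant difference would be fair evidence against all but very small effects. If they cannot, the same result says much less.

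**Working it through.** **Inputs from the article.** 30 families per arm (Interventions); two measurement times (Outcomes); d = 0.2, 0.5 and 0.8, and correlations 0.4, 0.6 and 0.9 (Sample size); d = 0.61 for child behaviour (Background).

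**Assumptions.** Two-sided alpha 5% and target power 80%, neither stated; d in units of the SD of a single score; all 30 per arm analysed.

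**Formulas.** For correlation r between before and after scores, the SD is multiplied by √(2(1−r)) for change scores and by √(1−r²) for baseline adjustment. The noncentrality is (d / SD factor) × √(n₁n₂/(n₁+n₂)). The square root is √15 = 3.873 for 30 v 30 and √20 = 4.472 for 60 v 30. Power is from the noncentral t distribution, with one degree of freedom lost for the baseline covariate.

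Example at r = 0.9, baseline-adjusted: the SD factor is √0.19 = 0.436, so the standardised effect is 0.2/0.436 = 0.459. The noncentrality is 0.459 × 3.873 = 1.78, against a critical value of about 2.0. Power is 42%.

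**The stated claim: power for d = 0.2**

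| Comparison | r = 0.4 | r = 0.6 | r = 0.9 |
|---|---|---|---|
| 30 v 30, change score | 11% | 14% | 40% |
| 30 v 30, baseline-adjusted | 13% | 16% | 42% |
| 60 v 30, baseline-adjusted | 16% | 20% | 53% |
| Before-after, one arm of 30 | 16% | 22% | 66% |
| Before-after, 60 trained families | 29% | 40% | 93% |
| Before-after, all 90 | 40% | 56% | 99% |

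The before-after rows use noncentrality 0.2√n / √(2(1−r)). A comparison of post scores alone, 30 v 30, has 12%.

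The most favourable between-arm case also falls short. With 60 v 30, r = 0.9, baseline adjustment and a one-sided 5% test, the noncentrality is 0.459 × 4.472 = 2.05, and power is about Φ(2.05 − 1.645) = Φ(0.41) = 66%.

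Detecting d = 0.2 with 80% power, baseline-adjusted, would take about 331, 253 or 76 families per arm at r = 0.4, 0.6 or 0.9.

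**Smallest difference detectable with 80% power, baseline-adjusted**

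| Comparison | r = 0.4 | r = 0.6 | r = 0.9 |
|---|---|---|---|
| 30 v 30 | 0.67 SD | 0.59 SD | 0.32 SD |
| 60 v 30 | 0.58 SD | 0.51 SD | 0.28 SD |

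**Larger effects, 30 v 30.**

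- d = 0.5 at r = 0.6: 57% (change score) to 66% (baseline-adjusted). At r = 0.9: 99%.
- d = 0.61, baseline-adjusted: 72% at r = 0.4 and 83% at r = 0.6. Pooled 60 v 30 at r = 0.4: 84%.
- d = 0.8 at r = 0.4: 79% to 91%, and more at higher r.

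**The correlation figures.** A raw covariance of 0.4 and an ICC of 0.9 can coexist if the variance is about 0.4/0.9 = 0.44. That still leaves 0.6 to 0.9 described as larger than 0.9. If 0.4 is the correlation, the ICC label is wrong; if 0.9 is, the contrast with the second scenario fails.

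**The case against.** **The section does not say that the comparison is between arms.** It speaks of an association in 90 participants with dependence between repeated measures, and before-after comparison within each format is an objective. At r = 0.9, the ICC printed beside d = 0.2, a before-after test has 99% power on all 90 families and 93% on the 60 trained ones. This stands, so a reader who infers that no analysis at any named correlation could detect d = 0.2 goes too far. But these tests have no control group, the one on all 90 mixes in untrained families, and a single format of 30 families has 66%.

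**The claim may use another index.** If d = 0.2 was entered as Cohen's f = 0.1 in the three-group by two-time interaction test, with noncentrality f² × 90 × 2/(1−r), power at r = 0.9 is 97%. With equal effects in the training arms, f is the difference in change divided by √18. So f = 0.1 means 0.42 SD (0.49 SD if one training arm has half the effect of the other), not 0.2. At r = 0.4 and 0.6 power is 31% and 45%. Separately, f = 0.2 at r = 0.4 gives 87%, but that is a difference of 0.2 × √18 = 0.85 SD. A reader might infer a mislabelled index; the documents do not show it.

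**The direction is not a demonstrated error.** Larger ICCs are paired with a larger minimum effect, the opposite of what change-score or baseline-adjusted analysis gives. For the between-groups term of a repeated-measures ANOVA, however, power does fall with correlation (f = 0.25: 70%, 64%, 56% at r = 0.4, 0.6, 0.9). Statistical methods allows both kinds of analysis. On that averaged-score reading, though, d = 0.2 has only 12 to 15% power between two arms.

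**The trial is not underpowered for everything.** A reader might infer that it cannot detect the effect in its own Background. The figures for d = 0.61 above show otherwise if baseline is adjusted for and r is 0.6 or more.

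**Conclusion.** The concern holds for the lower end of the claim and for the correlation figures. For between-arm comparisons the design does not detect d = 0.2 with usual power at any correlation named: 11 to 42% for two arms, and 16 to 53% for pooled training v usual care with baseline adjustment. The exact percentages rest on the assumed two-sided 5% and on d in raw-score SD units. The conclusion does not depend on sidedness, since one-sided testing in the most favourable contrast still gives only about 66%. The contradiction between 0.4, ICC = 0.9 and the larger ICCs needs no assumption.

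The upper end (d = 0.8) is not disputed, and d of about 0.6 is adequately powered at r = 0.6 or above with baseline adjustment. The pairing of larger ICCs with a larger minimum effect is an oddity that cannot be settled while the test is unnamed.

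**What to change.** Rewrite the Sample size section.

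- Delete the d = 0.2 claim and the pairing of 0.4 with ICC = 0.9.
- State the test, alpha, power and effect-size index.
- Give the detectable between-arm difference as a range over the assumed before-after correlation. Suggested text: *With 30 families per arm all analysed, two-sided 5% and 80% power, the smallest detectable difference between two arms, adjusted for baseline, is 0.67 SD at a before-after correlation of 0.4, 0.59 SD at 0.6 and 0.32 SD at 0.9. For both training arms together v usual care it is 0.58, 0.51 and 0.28 SD.*
- Add that these figures worsen if non-completers are excluded, as Analysis population and missing data says. With an assumed 24 per arm, 0.67 SD at a correlation of 0.4 becomes 0.76 SD.
- Add that a non-significant difference neither excludes a small effect nor shows that the two formats are equivalent.

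The change takes one paragraph and no extra participants. The cost is a less favourable stated sensitivity.

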### Recruitment

All groups will be invited to the Research Center of Impulsivity and Attention (NITIDA) at Hospital das Clínicas, UFMG–Brazil. NITIDA offers psychiatric outpatient care for children and adolescents with externalizing problems, in particular ADHD and ODD cases and being recognized by these services. On average, six new patients are screened per week and this project screening will continue until 100% of the expected sample is reached.

## Methods: Assignment of interventions

### Allocation

#### Sequence generation

Participants will be randomly assigned to either control or one of the experimental groups with a 1:1 allocation as per a computer-generated randomization schedule. The allocation sequence will be generated applying a permuted block design with random blocks, stratified by children’s age. Throughout the study, the randomization will be conducted by the computer technician without any influence of the principal investigators, raters or therapists.

#### Concealment mechanism

Allocation concealment will be ensured using sequentially numbered, opaque, sealed envelopes. The randomization code will be known by participants and therapists after all baseline measurements have been completed by the evaluator. The allocation will be revealed to the therapist and the participant the moment intervention is about to begin.

#### Implementation

All patients who give consent for participation and who fulfil the inclusion criteria will be randomized. Randomization will be requested by the staff member responsible for recruitment and clinical interviews and will be performed by the computer technician, both members of NITIDA. In return, the computer technician will send an answer form to the study therapist who is not involved in assessing the outcome of the study. This form will include a randomization number. Closed envelopes with printed randomization numbers on it will be available for the therapist. For every randomization number the corresponding code for the therapy group of the randomization list will be found inside the envelopes. The therapist will open the envelope and will find the treatment condition to be conducted in this patient. The therapist then gives the information about treatment allocation to the patient. Staff responsible for recruitment and symptom ratings is not allowed to receive information about the group allocation.

### Blinding

#### Blinding

Assessments will be conducted by a professional blind to treatment allocation. The assessor will go through an assessment training program with a specialist in the field. Due to the nature of the intervention neither participants nor the therapists can be blinded to allocation. Regardless of the allocation, the scales will be filled out by all participants on a tablet and the database will be fed automatically. The interviews and the cognitive measures collected by the appraiser will be passed on by himself to this database, which does not contain any information about the allocation and therefore it can be passed on to researchers.

Data management, statistician and staff responsible for recruitment and assessment will be blind to the type of intervention performed in each participant.

#### Emergency unblinding

The survey does not offer any risk to the participants, and therefore unblindings would not be applicable.

## Schedule of enrolment, interventions, and assessments

In Fig 3 the schedule of enrolment, interventions, and assessments can be seen.

**Fig 3 pone.0272516.g003:**
[figure not shown]
Schedule of enrolment, interventions, and assessments.

## Methods: Data collection, management, analysis

### Data collection methods

#### Data collection methods

An initial screening will be carried out by the outpatient team, trained in evaluation procedures by a specialist. In this screening, general data important to the research, such as the parents’ psychiatric history, for example, will be collected through an extensive anamnesis. In addition, the child’s psychiatric screening will be carried out through the K-SADS-PL, an interview based entirely on the diagnostic criteria of the latest edition of the DSM [10, 37]. Intelligence tests (matrices) will be applied to the child and the primary caregiver, both validated and with Brazilian normative data [43, 44].

After the screening, the included participants will undergo a first trial assessment, including a battery of scales that will be completed in the presence of an evaluator, on a notebook. The scales are self-reported (parents’ behavior; items 1, 2, 3, 4 and 5) or refer to the child’s behavior, according to the parents’ report (items 6, 7 and 8), besides the Brazilian Economic Classification Criterion [45].

ASRS—Adult Self-Report Scale (parents ADHD symptoms) [46].Depression, Anxiety and Stress Scale (DASS) [47].Perceived Stress Scale [48, 49].Parenting Styles and Dimensions Questionnaire (PSDQ) [38].World Health Organization Quality of Life abbreviated measure [41, 50].MTA-SNAP (children ADHD and ODD symptoms) [51].The Child and Adolescent Behavior Inventory (CABI) is a questionnaire useful for the preparation of screening for clinical evaluation [52].Kidscreen-52 to evaluate the quality of life of children [42].

After the participant completes the intervention, or the waiting time (six weeks, for the control group), the K-SADS will be reapplied and a battery of scales containing the same instruments (with the exception of the ASRS and DASS) must be completed by the main caregiver.

The interval between the pre-assessment and the beginning of the intervention, as well as the end of the intervention and the execution of the post-assessment, will be as small as possible, and cannot exceed a maximum period of 60 days. The deadline was considered for project feasibility, taking into account the need for flexibility in scheduling between the team and parents.

SNAP and ASRS check ADHD symptoms in children and adults, respectively, including ODD in children. Both instruments were translated into Portuguese with a methodology of translation, back-translation, evaluation of semantic equivalence, polling the target population and choice of final version [36, 46]. The SNAP validity and reliability were evaluated in a Brazilian study, in a sample of children with ADHD, which demonstrated good psychometric properties in this context [51]. In the same direction, ASRS-18 showed good psychometric properties [46], and the study showed that the instrument can be used as a complementary measure for the diagnosis of ADHD in adults. The Depression, Anxiety and Stress Scale (DASS) was adapted and validated for use in a Brazilian context [47], as well as the Perceived Stress Scale [48, 49] and the Parenting Styles and Dimensions Questionnaire (PSDQ) [38]. The Child and Adolescent Behavior Inventory (CABI) is a questionnaire designed to collect information from the parents of children and adolescents, being useful for the preparation of screening for clinical evaluation [52]. World Health Organization Quality of Life abbreviated measure showed a good performance concerning internal consistency, discriminant validity, criterion validity, concurrent validity and test-retest reliability, been an interesting option to evaluate quality of life in Brazil [41, 50]. Kidscreen-52 was chosen to evaluate the quality of life of children, specifically. The translation, cross-cultural adaptation and psychometric qualities of the KIDSCREEN-52 questionnaire were satisfactory, which makes its application in the Brazilian population feasible [42]. The Brazil Economic Classification Criterion or CCEB aims to be a unique way of assessing the purchasing power of consumer groups, dividing the market into economy classes. The instrument was built using statistical techniques that are based on collective data [45].

